## 3. Endpoints and Outcome Measures

(A)Qualitative psychological endpoints:

The baseline and follow-up at one and five years of the psychological features in the four groups of subjects (TTS patients, AMI patients, BC women, and HS) as well as subjects classified according to psychotherapeutic treatment will be assessed by the per-protocol psychometric tests, the two enrollment questionnaires (see below), and the Six Drawing test (6DT).

The following qualitative psychological variables will be evaluated at enrollment and the one-year follow-up:Perception of body and emotions; qualitative analysis will be performed with two questionnaires, administered to all participants: (1) Enrollment body perception questionnaire (Supplementary Material S1); (2) One-year follow-up body perception questionnaire (Supplementary Material S2).Subject’s memory of last week, last month, last year, and past years’ dreams only at enrollment. A qualitative analysis will be performed with two questionnaires, administered to all participants: (1) Enrollment dream questionnaire (Supplementary Material S3); (2) One-year follow-up dream questionnaire (Supplementary Material S4).6DT patterns characteristics

(B)Medical endpoints

Based on the patients’ choice after enrollment, if the size of groups undergoing psychotherapy and those declining is sufficient to allow comparisons, the following medical endpoints will be assessed:-In AMI and TTS pts: the cumulative incidence of new cardiac events (i.e., MI, revascularization, life-threatening ventricular arrhythmias, recurrence of typical angina pectoris, stroke, and death all-cause), plus the occurrence of any clinically significant new medical disorder (active diseases requiring hospitalization or chronic medical therapy, or that cause a transient or permanent physical limitation), at the one and five-year follow-up in patients undergoing psychotherapy plus standard medical therapy and those on standard medical therapy only.-In BC patients: the incidence of breast cancer relapse, metastasis, or the occurrence of any clinically significant new medical disorder (that is an active disease requiring hospitalization or chronic medical therapy, or that cause a transient or permanent physical limitation), at the one and five-year follow-up in patients undergoing psychotherapy plus standard therapy and those on standard therapy only.-In all pts: new hospital admissions.

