#### 3.2.2. Treatment Choice, Implementation, and Group Allocation

In the second phase, all pts with TTS, AMI, and BC will be asked to freely choose between ontopsychological STP along with standard medical therapy and, whenever indicated, rehabilitation therapy or medical therapy plus rehabilitation alone.

Therefore, this phase results in seven study groups: three groups of pts (AMI, TTS, and BC) undergoing psychotherapy, three groups of pts (AMI, TTS, and BC) on standard medical therapy, and one group of HS.

There will be four independent areas of research: (1) AMI pts following psychotherapy (AMI-PSY) will be compared with AMI pts, without psychotherapy (AMI-C); (2) TTS pts who will follow psychotherapy (TTS-PSY) will be compared with TTS pts without psychotherapy (TTS-C); (3) BC pts with psychotherapy (BC-PSY), will be compared with BC pts without psychotherapy (BC-C); (4) HS subjects, after the initial comparative evaluation with the other enrolled groups, will have an independent follow-up, where psychological data collected at enrollment will be compared with psychological data collected at one year and with clinical follow-up at five years.

Since the research is observational, it is not possible to foretell how many patients will choose psychotherapy plus medical therapy or standard medical care alone.

If balanced patient groups can be formed, statistical analysis evaluating differences between groups will be performed. Thus, it may be possible to evaluate how psychotherapy may impact the real world because patients will have a choice between psychotherapy plus medical care or medical care alone. It will also be possible to evaluate if psychotherapy might result in an improvement in psychological patterns compared to medical therapy alone, and how this can translate in an improvement in medical prognosis. Moreover, the patients’ choice might provide useful information to improve a more individualized therapy and hospital organization.

AMI-PSY and TTS-PSY patients will be referred to the outpatient clinic of Cardiac Psychology at San Filippo Neri Hospital in Rome; BC-PSY will be referred to the outpatient clinic of Psycho Oncology in the same hospital. Psychotherapy will be provided in individual sessions (maximum of ten) and five group meetings, as in the STEP IN AMI trial. Psychotherapy will be conducted by two expert psychotherapists trained in ontopsychology and psychosomatics.

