#### 3.2.3. Follow-Up

Follow-up is planned at one and five years with a comprehensive medical visit and yearly routine blood tests.

For AMI pts, echocardiography, an exercise stress test, or stress myocardial perfusion scintigraphy, will be performed when medically indicated.

For TTS pts echocardiography is timetabled at one month and six months after the acute phase, and yearly through the five-year follow-up when indicated.

For BC pts, history, physical examination, and mammography will be obtained at follow-up. Physical examination is planned every 3 to 6 months for the initial 3 years, every 6 to 12 months for years 4 and 5, and annually thereafter. For women who have undergone breast-conserving surgery, a post-treatment mammogram is scheduled 1 year after the initial mammogram and at least 6 months after completion of radiation therapy. Thereafter, unless otherwise indicated, a yearly mammogram will be scheduled. The use of complete blood counts, chemistry panels, bone scans, chest radiographs, liver and pelvic ultrasound, computed tomography scans, fluorodeoxyglucose–positron emission tomography scans, magnetic resonance imaging, and/or tumor markers (carcinoembryonic antigen, CA 15-3, and CA 27.29) are not recommended for routine follow-up in an otherwise asymptomatic patient with no specific findings on clinical examination [56].

At the one-year follow-up all patients and HS will be administered: (a) the same psychometric tests administered at enrollment; (b) two qualitative questionnaires, the 1-year follow-up body perception questionnaire (Supplementary Material S2), and the 1-year follow-up dream questionnaire (Supplementary Material S4); (c) the 6DT.

At the five-year follow-up, all psychometric tests will be administered to all of the groups.

Data will be recorded on paper case-report forms and transferred into an electronic database, with the principal investigator cross-checking consistency of data for all patients.

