## 4. Statistical Analysis

An external committee will evaluate the results in each phase of the research and the characteristics of each group will be analyzed. The qualitative results related to the 6DT, body perception questionnaire, and dream questionnaire at enrollment and the one-year follow-up. It is impossible to foretell the specific features of oneiric symbols and patterns before the study, as the research is a pilot study in the field of psychosomatics. The oneiric manual of the ontopsychological school [45] will be used as an initial reference point for the analysis and classification of dreams.

Unless otherwise specified, all study data will be analyzed on an intention-to-treat basis.

Event rates will be expressed as proportional incidences and as person−time incidence rates. Continuous variables for each of the study groups will be reported as means (with standard deviations or 95% confidence intervals) or as medians (lower quartile-upper quartile), as appropriate; categorical variables will be reported as absolute numbers and percentages. Continuous unpaired variables will be compared using the independent-sample Student’s t or Mann-Whitney U tests, and continuous paired variables will be compared using paired Student’s t or Wilcoxon tests, as appropriate. Categorical variables will be compared by Pearson’s chi-squared analysis or Fisher’s exact test, as indicated. The outcome incidence within each study group over long-term follow-up will be compared with Friedman’s test. Survival analysis will be performed using Cox proportional hazards ratios. Multivariable binary logistic regression analysis will be performed to appraise the independent predictive role of baseline characteristics on outcomes. Spearman’s rank correlation test will be performed to assess the correlation between variables. A *p* value < 0.05 will be considered statistically significant, with all inferential tests 2-tailed. Statistical analysis will be performed using the statistical software program SPSS, version 11.5 (SPSS Inc., Chicago, IL, USA).

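### Angina and new medical disorders in the AMI/TTS composite may be ascertained unequally, because psychotherapy patients have up to 15 more clinic contacts in an open, self-selected comparison

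*Protocol article*

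**What the plan says.** Section 3, Endpoints and Outcome Measures, part (B), defines the AMI/TTS composite as new cardiac events together with new medical disorders: "recurrence of typical angina pectoris, stroke, and death all-cause), plus the occurrence of any clinically significant new medical disorder". A new disorder qualifies if it needs admission or long-term treatment, or if it limits the patient physically, even for a time. New hospital admissions are a separate endpoint for all patients. The medical comparison is made only if the groups turn out large enough.

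Section 3.2.2 lets patients choose psychotherapy or not. For those who do: "Psychotherapy will be provided in individual sessions (maximum of ten) and five group meetings, as in the STEP IN AMI trial". The place is stated too: "AMI-PSY and TTS-PSY patients will be referred to the outpatient clinic of Cardiac Psychology at San Filippo Neri Hospital in Rome".

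Section 3.2.3 sets follow-up by disease, not by treatment choice: "Follow-up is planned at one and five years with a comprehensive medical visit and yearly routine blood tests". For AMI it adds: "For AMI pts, echocardiography, an exercise stress test, or stress myocardial perfusion scintigraphy, will be performed when medically indicated". For TTS, "echocardiography is timetabled at one month and six months after the acute phase, and yearly through the five-year follow-up when indicated". Breast cancer patients are examined every 3 to 6 months for three years. Section 2.3 refers all AMI patients to cardiac rehabilitation.

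Section 4 gives a review role to an outside body: "An external committee will evaluate the results in each phase of the research".

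**The concern.** Treatment choice is open, one group is seen more often, and part of the endpoint depends on whether a symptom is voiced and how it is judged. Typical angina is a symptom diagnosis. A passing limitation from a new disorder is easily forgotten by the one-year visit if nobody asks sooner. Section 2.1 also describes the therapy as working on how patients perceive their bodies, so it may change symptom reporting itself.

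A symptom mentioned in the clinic could lead to a referral, a test and a recorded event. That would add events to the psychotherapy group and hide a benefit or suggest harm. In the other direction, a classifier who knows that the patient chose psychotherapy may be slower to call chest pain typical angina or a new complaint clinically significant. That would suggest benefit. The multivariable regression in Section 4 adjusts for baseline characteristics, but this is error in measuring the outcome, which such adjustment does not reach.

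**Working it through.** **1. Contacts by treatment choice (AMI).**
- Both choices: medical visit at one and five years, yearly blood tests, rehabilitation referral, and imaging or stress testing when indicated.
- Psychotherapy only: 10 individual (maximum) + 5 group = up to 15 further hospital-clinic contacts.

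The scheduled medical follow-up is equal, so the difference is the sessions. In TTS and breast cancer the shared schedule is fuller (echocardiography at one and six months; examinations every 3 to 6 months), so the sessions should matter less there.

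**2. The plan's own figure.** Sample Sizing takes 43% against 78% for the one-year composite, 80% power and the 95% confidence level, giving 55 AMI patients. With unpooled variance, a two-sided test and an assumed 1:1 split:

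n per group = (1.960 + 0.842)² × (0.43 × 0.57 + 0.78 × 0.22) / 0.35² = 26.7, rounded up to 27, or 54 in total.

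This agrees with 55 to within one patient. The composite is therefore the endpoint on which the only sized group rests.

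**3. What unequal detection could do when there is no true effect.** The document gives no detection rates, so these are assumptions. Observed rate = true rate × detection. With a true rate of 60% in both groups:
- Psychotherapy, 95% detection: 0.60 × 0.95 = 0.57
- Control, 85% detection: 0.60 × 0.85 = 0.51, a difference of 6 points
- Control, 80% detection: 0.60 × 0.80 = 0.48, a difference of 9 points

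The spurious difference is the true rate times the detection gap. If the common true rate runs from 43% to 78%, it lies between 0.43 × 0.10 = 4.3 points and 0.78 × 0.15 = 11.7 points.

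**4. Effect on the test.** Take a true rate of 60% in both groups, full detection under psychotherapy, 27.5 patients per group and a pooled two-sided test at 5%. The chance of a false significant result is:

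| Control detection | Observed rates | Rejection probability |
|---|---|---|
| 100% | 60% v 60% | 0.050 |
| 95% | 60% v 57% | 0.056 |
| 90% | 60% v 54% | 0.073 |
| 80% | 60% v 48% | 0.143 |

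**5. The opposite bias.** Nothing in the document allows the effect of unmasked judgement to be sized, so no figure is given and no net direction can be stated.

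**The case against.** Several points on the other side stand.

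- A reader might infer that controls are seen only at one and five years. They are not. Section 3.2.3 gives both choices the same disease-based schedule, and Section 2.3 adds rehabilitation referral for every AMI patient.
- A reader might infer that detection does differ. The sessions are run by psychotherapists, and nothing says that medical events are recorded there. The route from a symptom voiced in a session to a test and an event is plausible but not documented, so detection may differ and no more can be said.
- A reader might apply the same detection rates to the planning figures: 0.43 × 0.95 = 40.9% against 0.78 × 0.80 = 62.4% or 0.78 × 0.85 = 66.3%, with power (unpooled test, 27 against 28) falling from 81% to 37% or 50%. That is not supported. The 43% and 78% are taken from results observed in STEP-IN-AMI, and the sessions follow that trial. Any detection effect of the sessions is largely in those rates already and would be counted twice.
- A condensed article may leave adjudication detail to the full protocol, so silence on masking is not itself a fault.
- Moving psychiatric diagnoses out of the composite would be a preference. The depression inventory is given to everyone at the same times.
- The comparison is conditional on group sizes, and Section 5 describes the study as designed primarily for qualitative analysis at enrolment.

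These points limit the strength of the concern without removing it. The shared follow-up goes to both groups, so the additional sessions remain a difference. The soft components, the extra contact and the indication-driven testing are all stated design features.

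**Conclusion.** The point holds as a risk built into the stated design. Ascertainment of typical angina and new medical disorders may differ by treatment choice, chiefly in AMI. The size is unknown: 57% against 48–51% is an illustration that rests on an assumed 60% true incidence in both groups and assumed detection of 95% against 80–85%. The test-level figures further assume near-equal groups, whereas the plan says the split cannot be foretold, and one of the four AMI patients enrolled so far chose psychotherapy. Because the two possible biases oppose each other, a beneficial, null or harmful result on the composite would be hard to interpret as the endpoint stands. The change is worth making and is cheap.

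**What to change.** In Section 3(B) and Section 4, state three things.

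1. A composite event counts only if it is captured at a scheduled medical visit or in medical records, by the same procedure whichever treatment was chosen. An event known only from a therapy session does not count.
2. The existing external committee classifies typical angina and new medical disorder from summaries with treatment choice and therapy notes removed.
3. Death, MI and stroke, which depend little on contact, are reported as a separate set beside the composite and the already planned hospital admissions. Revascularisation stays out of this set because it can follow from indication-driven testing.

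The cost is preparing masked summaries and losing a few minor events known only from sessions. The hard set will contain few events at this sample size, so it supports interpretation of the composite and cannot replace it. No new visits are needed. At the time of the article 4 of 55 AMI patients had been enrolled, so the rule could still cover nearly all AMI data.

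### The breast cancer composite omits death, so a woman who dies with no earlier counted event is event-free; whether recurrent Takotsubo counts is also left unclear

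*Protocol article*

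**What the plan says.** All the endpoint definitions stand in the protocol article, section 3, part (B).

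- **AMI and TTS patients** share one composite. Its first part is "new cardiac events (i.e., MI, revascularization, life-threatening ventricular arrhythmias, recurrence of typical angina pectoris, stroke, and death all-cause"; its second part is "plus the occurrence of any clinically significant new medical disorder (active diseases requiring hospitalization or chronic medical therapy", or a disorder that limits the patient physically.
- **BC patients** have their own composite: "In BC patients: the incidence of breast cancer relapse, metastasis, or the occurrence of any clinically significant new medical disorder". The last component is explained as "that is an active disease requiring hospitalization or chronic medical therapy, or that cause a transient or permanent physical limitation".
- **All patient groups** have one further, separate endpoint: "In all pts: new hospital admissions".

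Section 3.2.3 sets the assessment times: "Follow-up is planned at one and five years with a comprehensive medical visit and yearly routine blood tests". Section 4 says that event rates will be given as proportions and as person-time rates, that analysis is by intention to treat unless otherwise specified, and that "Survival analysis will be performed using Cox proportional hazards ratios". It does not say to which endpoint the Cox model applies or how deaths enter it.

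**The concern.** An outcome used to judge prognosis should not let a death pass as a good result. The two composites stand next to each other. One counts death from any cause and the other does not, with no reason given for the difference. If deaths without an earlier counted event were more frequent in one BC arm, that arm's incidence would be understated by more than the other's, and the comparison of psychotherapy with standard care would be distorted. The direction cannot be known in advance.

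The second, weaker issue is recurrence of the index disease. AMI patients have new MI counted and BC patients have relapse counted. For TTS patients the corresponding event is not named, although section 2.2.1 enrolls them without critical coronary stenosis, so revascularization and typical angina fit them less well than they fit AMI patients.

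**Working it through.** **1. Does any component capture a BC death?** The components can be checked one by one for a woman who dies with no earlier recorded event.

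| Component or endpoint | Captures her death? |
|---|---|
| Relapse | No |
| Metastasis | No |
| New medical disorder | No: it is defined as an active disease with stated consequences, and death is not among them |
| New hospital admission | Not a component of the composite, and a death outside hospital is not an admission |

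No other section adds death for BC. Under intention to treat she stays in the denominator of the one- and five-year proportions and adds nothing to the numerator. In the person-time rate her time ends without an event. In a Cox model her death could be an event, a censoring or a competing event; the article does not say which.

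**2. Size per uncounted death.** The plan gives no figure of its own to reproduce here: the section on sample sizing sets 55 BC patients to match the AMI group, without a calculation or an event rate.

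Inputs: planned BC patients 55 (sample sizing); 5 of the first 11 chose psychotherapy (Enrollment Status).

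- Psychotherapy arm: 55 × 5/11 = 25. Other arm: 55 − 25 = 30.
- Shift in an arm's incidence per uncounted death = 100/n points.
- 100/25 = 4.0 points; 100/30 = 3.3 points.

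The split rests on 11 women and is an assumption. An even split gives 100/27.5 = 3.6 points. A less even one, say 15 and 40, gives 100/15 = 6.7 and 100/40 = 2.5 points.

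The total effect is this shift multiplied by the number of deaths with no prior counted event. The article gives no death rate, so the total cannot be derived.

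**3. TTS recurrence.** The cardiac list is introduced by i.e., so it is closed, and recurrence of TTS is not on it. Two other routes remain:

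- *The new-disorder clause.* A recurrence of the enrolling disease is not plainly new. Yet the Introduction says that TTS usually resolves by itself in survivors, so a later episode could be read as a fresh active disease. Both readings are possible.
- *New hospital admissions.* A hospitalized recurrence counts here, but outside the composite.

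The wording therefore leaves the composite status of a TTS recurrence to the adjudicator.

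**The case against.** **The BC gap is narrow.** The new-disorder component is broad: it takes in anything that needs hospitalization or chronic therapy, or that limits the patient even transiently. Many BC deaths will follow an event that already counts. The women have non-metastatic disease and are aged 30 to 75, and life-threatening conditions are excluded. All this stands and limits the point to deaths without a prior counted event. It does not remove them over five years.

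**The handling of deaths belongs in an analysis plan that is not shown.** This is fair for censoring and competing-risk rules. A reader might infer that the Cox model will censor these deaths and so be biased. Section 4 does not say so, and censoring deaths can validly target a cause-specific hazard. The component list is different: the article itself states it, and the objection is to what it states.

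**Recurrent TTS is not ignored.** A reader might conclude that the TTS comparison misses the event most specific to that disease. That goes too far, because a hospitalized recurrence enters the separate admissions endpoint and may be adjudicated into the composite. What stands is an ambiguity.

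**The comparisons may never be made.** Section 3(B) makes the medical endpoints depend on sufficient group sizes, and section 3.2.2 makes between-group testing depend on balanced groups. The sample-sizing section calls the non-AMI groups exploratory. This also stands and lowers the severity.

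**Conclusion.** The BC composite has a definitional gap: a death with no earlier counted event is scored as event-free in the one- and five-year proportions, contrary to the rule applied to AMI and TTS patients. Each such death moves an arm's incidence by about 3 to 4 points if the arms are about 25 and 30, a split extrapolated from 11 women.

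Two stronger figures are tempting and are not supported. Three such deaths all in the arm of 25 would give 3 × 4.0 = 12 points, but neither that number nor its placement in one arm has a basis in the article. For TTS, applying 15 of 19 to 30 patients gives 30 × 15/19 = 23.7, so about 24 and 6, and one uncounted recurrence in the arm of 6 would be 100/6 = 16.7 points. A split that uneven may fail the plan's own condition of balanced groups, and the recurrence might be counted after all.

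The TTS point is secondary and concerns clarity. Overall severity is moderate: the comparisons concerned are exploratory and conditional, and the AMI composite, the only one used for sizing, already includes both MI and death.

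**What to change.** 1. Define the BC composite as relapse, metastasis, all-cause death, or clinically significant new medical disorder. Use this definition for the one- and five-year proportions, the person-time rates and any Cox model.
2. Add recurrence of Takotsubo syndrome to the cardiac-event list for TTS patients, so that its status does not depend on whether it is judged new.

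The cost is two wording changes. Admissions are already an endpoint for all patients. The article does not expressly mention tracking vital status in BC, so the change should say that date of death is recorded; the planned five-year follow-up should establish this in any case. At the reported status 19 + 11 + 4 = 34 of 140 patients were enrolled. The change should be made before outcomes are known, since afterwards it would be a post hoc redefinition of the endpoint.
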